### Standardized anesthesia

All patients were instructed not to eat for 8 h or to drink for 4 h prior to procedures, and no preoperative drugs were administered. Routine monitoring devices were set up to monitor electrocardiogram, heart rate (HR), noninvasive blood pressure (BP), oxygen saturation (SpO_2_), respiratory rate (RR), and partial pressure of end-tidal carbon dioxide (PetCO_2_). O_2_ at 2 L/min was applied through a nasal catheter, and intravenous access was opened. General anesthesia was induced with propofol (2 mg/kg), sufentanil (0.2 μg/kg), and cisatracurium (0.15 mg/kg). After adequate jaw relaxation was attained, tracheal intubation was performed, and each patient was mechanically ventilated with a tidal volume and ventilation rate adjusted to maintain the pressure of end-tidal carbon dioxide (ETCO2) at 35–45 mmHg. The anesthesiologist adjusted the intravenous speed of remifentanil and propofol according to hemodynamic parameters and BIS (BIS monitor; Aspect Medical System, Newton, MA). In the LBIS group, BIS was maintained between 40 and 50 during the operation, and in the HBIS group, BIS was maintained between 50 and 60 for maintenance. Both groups received 0.15–0.2 μg/kg/min for remifentanil and together with inhaled 50% air and 50% oxygen (O_2_) at a fresh gas flow rate of 2 L/min. Cisatracurium (0.05 mg/kg) was intermittently used for muscle relaxation. Ten minutes before the end of the surgery, stop all anesthetic infusions, and after extubating, the patients were transferred to the PACU for continuous monitoring.

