### Observation indicators {12}

#### General data

The following patient data were collected from the anesthetic records: age, gender, height, weight, body mass index (BMI), American Society of Anesthesiologists physical status (ASA), duration of falling asleep, duration of surgery, duration of anesthesia, duration of recovery to consciousness (time between withdrawal of drugs and orientation of patients to time, place, and person), and drugs used for anesthetic management. The Hospital Anxiety and Depression Scale (HADS) is a self-report questionnaire used to assess the anxiety and depression status of participants during the perioperative period (Fig. 2). We used the Japanese version of HADS in this study. HADS consists of two subscales: anxiety (HADS-A) and depression (HADS-D). Each score consists of 7 questions, ranging from 0 to 3 (each score is 0–21), depending on the probability of the psychological problem described. Patients with a score of 11 or higher can be classified as possibly significant [13, 14]. We evaluated HADS score of patients the day before surgery.

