#### Intraoperative data

Mean arterial pressure (MAP) and HR of each patient were recorded at 5 min after entering the operation room (T0), after anesthesia induces to fall asleep (T1), at the end of the operation (T2), recovery from anesthesia (T3), and exiting from the operation room (T4). Record the total amount of propofol used during surgery.

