## Discussion

Dreams are a remarkable experiment in psychology and neuroscience, conducted every night in every sleeping person. They show that the human brain, disconnected from the environment, can generate an entire world of conscious experiences by itself. The occurrence of dreams is also one of the common phenomena of anesthesia and sedation. The occurrence of dreams during general anesthesia has been reported in the literature. The dream after anesthesia refers to the patient’s experience after the induction of anesthesia to the beginning of the waking phase. Domestic scholars have conducted research on the effects of short-town intravenous anesthesia and specific anesthetics on dreams of adult receiving surgery, which found that the incidence of adult dreams is about 18% ~ 49.7% [19, 20]. Among them, different anesthesia drugs, operation site, operation time, and so on are all the influential factors leading to the occurrence of dreams. Previous hypothesis also thought that dreaming occurs intraoperatively and is related to light or inadequate anesthesia [21, 22]. In order to verify this previous hypothesis, we designed a randomized, observer- and patient-blinded, controlled clinical trial, which compared the effects of different maintenance doses of propofol on patients’ dreams and analyzed the related factors affecting dreams. A recent study has shown that depression and anxiety assessed by Beck anxiety/depression inventory can predict a negative dream during natural sleep [23]. Similarly, we assessed preoperative anxiety level to see if patients with different preoperative anxiety states were associated with different dreams generated during anesthesia. In our trial, the subjective outcomes including HADS, Ramsay scale, modified Brice questionnaire, and awareness classification will be assessed. In this way, the effect of different dose of propofol maintained during the surgery on the incidence of dreaming of patients will be evaluated from multiple perspectives.

Our study has some limitations. First, since all the patients were hospitalized, we only scored the preoperative anxiety during the perioperative period but did not evaluate the daily long-term psychological base state and the degree of dreaming under natural sleep. Second, the study was part of a single-center survey, multicenter survey still need to be studied.

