## Conclusion

In conclusion, the results of our trial are expected to demonstrate the proportion of patients in the HBIS group who had dreams during the surgery vs that of patients in the LBIS group and whether there are patient-reported awareness during anesthesia. Through all the patients who reported dreaming during the surgery, we are aimed to explore the proportion of those who reported having pleasant dreams in the LBIS group vs that of patients in the HBIS group, to further compare whether there is a difference in the dosage of propofol between the two groups, and to analyze the factors associated with different postoperative dream generation. In summary, according to the study results, we hope to provide a basis for good perioperative experience and better postoperative recovery of patients in clinical practice.

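### Propofol exposure is specified only as a total amount and achieved BIS is not among the listed data, so the dream-status dose comparison is confounded by operation length and arm separation is not shown directly

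*Protocol article*

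**What the plan says.** The Abstract and Introduction ask whether dreaming is related to the maintenance dose of general anesthetics. The arms are BIS 40-50 and BIS 50-60 (Randomization, study intervention, and blinding). The dose measure, under Intraoperative data, is a total: "Record the total amount of propofol used during surgery". The Sample size section uses total propofol in dreamers and non-dreamers from an earlier study, 337 ± 161 mg and 259 ± 145 mg. The Conclusion also plans "to further compare whether there is a difference in the dosage of propofol between the two groups", and the Statistical analysis section plans logistic regression for predictors of dreaming.

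General data lists weight, and also "duration of surgery, duration of anesthesia, duration of recovery to consciousness". Neither that list nor the intraoperative and postoperative lists include achieved BIS. The Discussion says that "operation site, operation time, and so on are all the influential factors leading to the occurrence of dreams".

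**The concern.** Total mg is not the maintenance dose that the trial asks about. It rises with a heavier patient or a longer operation at an unchanged infusion rate. The eligibility criteria do not restrict operation length, and the article itself counts operation time among the causes of dreaming. An association between total mg and dreaming could therefore reflect longer surgery and say nothing about depth of anesthesia.

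The second gap concerns the randomised quantity. The two bands meet at 50, so patients in different arms can have almost the same BIS. Without achieved BIS by arm, a null result on dreaming is hard to tell apart from arms that did not separate.

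**Working it through.** **What total mg contains.** With rate r (mg/kg/h), weight w (kg) and maintenance time t (h), total mg = r × w × t, plus 2 × w if the 2 mg/kg induction dose under Standardized anesthesia is counted. The article does not say whether it is. Purely as an illustration, take r = 5 mg/kg/h with the bolus counted:

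- 50 kg for 1 h: 5 × 50 × 1 + 100 = 350 mg.
- 80 kg for 4 h: 5 × 80 × 4 + 160 = 1760 mg.

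That is a five-fold range at one rate. These are two extreme patients, not group means.

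**Dream-status comparison.** Operation time raises total mg by arithmetic and, by the Discussion's account, affects dreaming, so it confounds this non-randomised contrast.

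- The sample-size figures have ratio 337/259 = 1.30. At equal rate and weight, with no bolus counted, a 30% longer infusion explains the whole 78 mg.
- With a 2 mg/kg bolus counted and an assumed weight of 65 kg (130 mg), the ratio of maintenance amounts is (337 − 130)/(259 − 130) = 207/129 = 1.60, so a 60% longer infusion would be needed.
- Dreamers received more propofol in total, while the hypothesis ties dreaming to light anesthesia. Total mg cannot say whether that reflects depth or duration.

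**The plan's own figure.** The pooled SD is √((161² + 145²)/2) = 153.2 mg, so d = 78/153.2 = 0.51. A two-sided t test at 80% power needs 62 evaluable per group before withdrawals, not the stated 56. That is a separate matter and does not bear on this point.

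**Between-arm dose comparison.** Randomisation balances weight and duration in expectation, so the cost is precision. Assumptions, none from the documents: CV of rate 20%, of weight 17%, of duration 30%, 50% or 70%; independent factors; bolus ignored; a true rate 20% lower in the high-BIS arm; 62 per arm; two-sided t test at 0.05.

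CV of total = √((1 + 0.20²)(1 + 0.17²)(1 + CV_duration²) − 1), and d = 0.20/CV.

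| Duration CV | CV of total mg | Power, equal SD | Power, SD proportional to mean |
|---|---|---|---|
| 30% | 0.41 | 0.77 | 0.85 |
| 50% | 0.58 | 0.48 | 0.56 |
| 70% | 0.77 | 0.30 | 0.35 |

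On the rate itself, d = 0.20/0.20 = 1.0 and power exceeds 0.99.

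**Sensitivity.**

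- Other assumptions (rate CV 25%, weight CV 15%, mean weight 65 kg, mean duration 1 h, rate ratio 1.2, bolus counted in the total, duration CV 20%, 40% and 60%) give 0.75, 0.48 and 0.30 on total mg, against 0.98 on the rate.
- Lognormal data with the first set of CVs give, by t test, about 0.86, 0.56 and 0.36 and, by Wilcoxon, about 0.86, 0.61 and 0.41.
- Leaving the bolus in the normalised dose lowers its power to about 0.96 (mean duration 1 h, CV 50%).
- The article's own figures give CVs of 145/259 = 0.56 and 161/337 = 0.48. With these, power on total mg is 0.51 and 0.64 (equal SD), or 0.59 and 0.72 (SD proportional to mean).

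**The case against.** **The normalising data exist.** Weight and the durations of surgery and anesthesia are collected, and the Conclusion speaks of propofol dosage without a unit. An average mg/kg/h can be derived, and the regression covariates may be fixed in a fuller plan. This stands: the data are not lacking. But the only dose quantity the article names, and the one it sizes the trial on, is the unadjusted total.

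**The arm comparison is randomised.** A reader might infer that the low- versus high-BIS dose comparison is confounded too. It is not: weight and duration add noise there, not bias. The comparison of dreaming proportions between arms does not use propofol dose at all.

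**BIS was monitored in every patient.** It guided titration, compliance was to be supervised during maintenance, and missing intraoperative data can be taken from electronic files. A reader might infer that BIS was never recorded, or that separation cannot be shown at all. The text supports neither: a fuller record form may exist, and a normalised rate by arm would be indirect evidence of separation. What stands is that no section names an achieved-BIS measure.

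**Time points T0 to T4.** A reader might take these as proof that nothing was captured during maintenance. They are the schedule for arterial pressure and heart rate only, and say nothing about BIS capture.

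**The power figures rest on assumptions.** This is fair. Only the direction and rough size should be relied on.

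**Conclusion.** The point holds in a limited form.

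- **Dose measure.** A total-mg comparison of dreamers and non-dreamers, as written, is confounded by operation length on the article's own account. That conclusion needs no assumed figure. The between-arm dose comparison remains unbiased but is inefficient: roughly 30-85% power on total mg for a 20% rate difference, against over 95% on a normalised rate, conditional on the assumed CVs.
- **BIS.** Achieved BIS is absent from the listed data, so separation of two adjoining bands cannot be shown directly from that list.

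This is a cheap improvement to how the results can be read. It does not invalidate the randomised comparison of dreaming.

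**What to change.** 1. For the between-arm and dream-status comparisons, analyse maintenance propofol in mg/kg/h, using the weight and durations already collected. Exclude the induction bolus, first establishing whether the recorded total includes it. Report total mg descriptively.
2. Define the maintenance window as end of induction to infusion stop. Duration of surgery alone will not serve as the denominator, given the instruction "Ten minutes before the end of the surgery, stop all anesthetic infusions".
3. Where retrievable from the monitor or anesthetic record, derive each patient's mean BIS and share of maintenance time in the assigned band. Report both by arm before interpreting the dreaming result, with the number of patients lacking a usable trend.

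The dream-status comparison stays observational even after normalisation and should be described so.

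**Cost.** Item 1 needs no new measurements; exact infusion times and BIS need a small extraction from existing records. Some BIS trends may be irretrievable. Trial status reports recruitment finished and data collection still in progress, so on that status the extraction could still be added. No change to patient management is involved.

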#### Postoperative data

Record the Ramsay score during orientation recovery (Ramsay sedation scale: 1 = patient anxious, agitated or restless or both; 2 = patient cooperative, oriented, tranquil, and alert; 3 = patient responds to commands; 4 = asleep, but with brisk response to light glabellar tap or loud auditory stimulus; 5 = asleep, sluggish response to light glabellar tap or loud auditory stimulus; 6 = asleep, shows no response to light glabellar tap or loud auditory stimulus) [15]. Record the patients’ satisfaction level in the PACU: fairly dissatisfied, medium satisfied, most satisfied, very satisfied.

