### Statistical analysis

#### Sample size

In this trial, according to the previous study [18], the total dose of propofol in the dream group was 337 ± 161 mg and by 259 ± 145 mg in the no dream group. Using a *t* test of two independent samples in PASS for calculation, the withdrawal rate is 20% to ensure that the results are statistically different (*α* = 0.05, 1-*β* = 0.8); therefore, each group requires 56 subjects. To improve the reliability of the trial, we will recruit a total of 124 patients, with 62 in each group.

The SPSS 20.0 statistical software (SPSS, Inc., Chicago, IL, USA) and GraphPad Prism 6.0 software were used for data analysis. Continuous data were tested for normality. Normally distributed data were summarized using mean and standard deviation and were compared using unpaired two-tailed *t*-tests. Skewed data were summarized using.median and range and were compared using Wilcoxon rank-sum tests. Categorical data were summarized using number (%) and were compared using *Χ*^2^ test or Fisher’sexact tests. Logistic regression was used to determine predictors of dreaming and correlation with dream quality. Categorical variables were created from continuous variables in applicable cases. A *P* value of less than 0.05 was considered statistically significant.

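### PACU satisfaction is recorded on four graded levels, but the stated test rules have no place for ordered categories: fix the level order and name an ordinal test (minor).

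*Protocol article*

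**What the plan says.** Under Postoperative data, the protocol article has satisfaction in the PACU recorded on four levels: "fairly dissatisfied, medium satisfied, most satisfied, very satisfied". It gives the four labels no numerical codes and does not say which end of the list is best.

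The Statistical analysis section sets its group comparisons by data type:

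- **Continuous data.** "Continuous data were tested for normality". Normal data go to "unpaired two-tailed" t-tests. Skewed data "were compared using Wilcoxon rank-sum tests".
- **Categorical data.** "Categorical data were summarized using number (%) and were compared using" the chi-square or Fisher's exact test.

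There is no third rule for ordered categories, and no section assigns a test to satisfaction by name. The significance rule is a P "value of less than 0.05 was considered statistically significant". On size, "we will recruit a total of 124 patients, with 62 in each group".

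**The concern.** A four-label verbal item, naturally reported as counts and percentages, fits the categorical rule better than the continuous one. A 2×4 chi-square or Fisher test ignores the grading: shuffle the four labels and the P value is the same. The chi-square spreads its sensitivity over 3 degrees of freedom, whereas a shift towards more or less satisfaction is essentially one dimension. Two things are at stake:

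- a real shift in satisfaction is more likely to be missed;
- a significant result need not mean that one arm was more satisfied than the other.

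The printed list raises a second problem. It places *most satisfied* before *very satisfied*, although in ordinary English *most* outranks *very*. This may come from translation. Any test that uses the order needs the order settled first, and if it is left open it could be chosen after the results are seen.

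**Working it through.** **No figure of the plan to reproduce.** The sample-size paragraph is built on propofol dose. The article states no expected distribution, effect size or power for satisfaction.

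**Inputs from the protocol article.** Four levels, so a 2×4 table with (2−1)×(4−1) = 3 df; 62 per arm; significance level 0.05. Two-sided testing is stated for the t-test and assumed here for the rank test.

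**Inputs assumed.** Five satisfaction distributions for one arm (lowest to highest level, %): 25/25/25/25, 5/15/40/40, 10/20/40/30, 2/8/30/60 and 5/25/45/25. The other arm is shifted by a common odds ratio (OR) of 1.5 to 3 at every cut of the scale. This is what a consistent shift means below.

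**Step 1: one case by hand.** Take 10/20/40/30 and OR 2.

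- Cumulative proportions 0.10, 0.30, 0.70 have odds 0.111, 0.429, 2.333. Halved, these are 0.056, 0.214, 1.167, which give cumulative proportions 0.053, 0.176, 0.538. The shifted arm is therefore 5.3/12.4/36.2/46.2%.
- Noncentrality of the 2×4 chi-square with n per arm: λ = n × Σ(p−q)²/(p+q) = 62 × (0.0147 + 0.0179 + 0.0019 + 0.0343) = 62 × 0.0688 ≈ 4.26.
- On 3 df (critical value 7.815) this λ gives power of about 38%. If the same λ is concentrated on 1 df (critical value 3.841), power is about 54%.

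Simulation of this case gives 37.6% for chi-square and 54.4% for the rank test.

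**Step 2: the general relation.** With equal noncentrality on 1 and 3 df, where λ = (1.960 + z for the power)²:

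| Power on 1 df | Power on 3 df | Points lost | Relative loss |
|---|---|---|---|
| 30% | 19.7% | 10.3 | 34% |
| 50% | 34.5% | 15.5 | 31% |
| 80% | 64.5% | 15.5 | 19% |
| 90% | 78.4% | 11.6 | 13% |

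**Step 3: simulation.** 40,000 trials per setting, 62 per arm, Pearson 2×4 chi-square against the tie-corrected Wilcoxon rank-sum test. Ranges are over the five distributions:

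| OR | Rank test | Chi-square | Points lost | Relative loss |
|---|---|---|---|---|
| 1.5 | 19–24% | 12–16% | 8 | 34–40% |
| 2.0 | 44–57% | 28–41% | 16–17 | 29–35% |
| 2.5 | 64–80% | 46–64% | 16–18 | 20–28% |
| 3.0 | 78–92% | 61–81% | 11–16 | 12–21% |

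A narrower set of three assumed distributions (5/20/40/35, 10/25/35/30, 5/15/30/50) gives 33–38% for chi-square against 50–56% for the rank test at OR 2, and 69–79% against 85–90% at OR 3.

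With 20% withdrawal, 62 × 0.8 ≈ 50 remain per arm. At OR 2, power is then 23–33% for chi-square against 37–48% for the rank test.

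**Step 4: type I error.** With no difference at 62 per arm, the rank test rejects in 5.0–5.1% of trials and chi-square in 3.9–5.0%. The low value belongs to the most lopsided distribution.

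**Step 5: where the advantage reverses.** For 10/20/40/30 against 20/10/30/40%, a difference without direction, chi-square has 51% power and the rank test 7%. For 5/15/50/30 against 5/15/30/50%, where all movement is between the top two levels, the figures are 54% and 39%.

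**Step 6: cost of a wrong order.** If the top two labels are ranked the wrong way round, rank-test power at OR 2 falls from 54% to about 5% with 5/20/40/35. Over all the distributions above, the mis-ordered power at OR 2 runs from 5% to 30%. Chi-square is unaffected.

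**The case against.** Four points weigh on the other side.

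- **The assignment to chi-square is inferred.** The article does not name a test for satisfaction, and an analysis plan that is not shown could name another. This stands, and the point is worded accordingly. What the article does state is a complete-looking pair of rules into which an ordered item fits badly.
- **Chi-square is a valid test and does not depend on the order of the labels.** This stands. The issue is efficiency and interpretation, not bias. Step 6 shows that a rank test with the wrong order would be worse than the chi-square, so the order has to come first.
- **The simulated shifts favour the rank test.** This stands too: Step 5 shows reversals. But a question about more or less satisfaction is directional, and the unordered test does not answer it.
- **Satisfaction is not central.** It is a keyword, and the Introduction says dreaming may lower it. Yet it is missing from the abstract's methods, from the Discussion's list of subjective outcomes and from the comparisons in the Conclusion, and it does not set the sample size. The Introduction also links satisfaction with dreaming, whereas the figures here compare the two BIS arms. This limits the weight of the point.

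Three stronger readings are tempting, and the documents do not support them. A reader might infer that a third of the power is lost: that fits only odds ratios of about 1.5 to 2, and the relative loss is about one fifth where the rank test has 80% power. A reader might say that the plan already provides the right test: its Wilcoxon test is written for skewed data within the continuous rule, so using it here extends that rule. And a reader might carry the argument over to the three-level feeling about the dream: the Conclusion frames that aim as the proportion with pleasant dreams, for which a chi-square or Fisher test is suitable.

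**Conclusion.** The point holds as a minor improvement. The stated rules make no provision for ordered categories, and their plain reading sends a graded satisfaction item to a test that ignores the grading. For a consistent shift at 62 per arm the cost is about 8 to 18 percentage points of power. That size depends on the assumed distributions and on odds ratios of 1.5 to 3, since the documents supply neither. It does not hold for every pattern of difference. The unclear order of the top two labels is visible in the text, needs no assumption, and must be settled before any ordinal analysis.

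**What to change.** Before allocation is opened:

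1. State the order of the four satisfaction levels, lowest to highest, taken from the original-language form, and correct the English labels if the translation is at fault.
2. State that the arms are compared on satisfaction with the Wilcoxon rank-sum test, or with a proportional-odds model reporting an odds ratio with its 95% confidence interval. Keep number (%) per level as the summary, so that a pattern without a direction remains visible.

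The cost is one or two sentences, with no new data and no change to sample size. The timing allows it: Trial status says data collection is in progress, and the randomization section keeps allocation closed until the analysis.
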